### Randomization and allocation concealment

Eligible participants will be randomized into one of two groups: the intervention group or the control group (1:1), using block random method and the block size is 6. The randomization sequence will be prepared by a professional statistician ([name]) with the SAS9.3 software, who is not involved in assessment, treatment, or analysis of the study, to ensure balance in baseline BP across the groups. When an eligible participant needed to receive a random group, the random number and the group assignment will be sent from the random number administrator to the recruiter via phone or short message.

The participants and study staff interacting with participants will not be blinded to group assignment in the trial. The outcome assessors and trial statisticians, who will not be involved in the intervention, will be blinded.

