### Outcomes

#### Primary outcome

The primary outcome will be the change in mean SBP from baseline to 12 weeks.

BP will be measured as proposed by the 2018 Chinese Guidelines for Prevention and Treatment of Hypertension [10]. Participants will be asked to avoid exercise, alcohol, cigarettes, and coffee/tea for at least 30 min before the BP measurement. BP will be measured with the participant in a seated position after 5 min of quiet rest. Participants will be required to take blood pressure measurement. A digital BP monitor (HEM-7136, OMRON Corporation, Kyoto, Japan) with suitable cuff size will be used. Clinicians will record three sequential BP readings at 5-min intervals, and the final BP will be calculated by removing the initial reading and calculating the mean from the two remaining readings.

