### Statistical methods

#### Sample size

This pilot study aims to assess the effectiveness and safety of TEAS combined with lifestyle modification for high-normal BP and determine the feasibility of a further large clinical trial. The minimum sample size for exploratory trials is 20 to 30 per group according to Provisions for Drug Registration in China. It is generally accepted that at least 30 participants are required for a pilot study [33]. We selected the maximum of 30 participants, and the sample size of 60 participants was determined. The results of this study will facilitate the calculation of an appropriate sample size for further randomized clinical trials.

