#### Statistical analysis

Analysis will be carried out on an intention-to-treat (ITT) basis and will be performed using SPSS 23.0 statistical software (IBM SPSS Statistics, New York, USA) with a 2-sided *P* value of less than 0.05 considered significant. The measurement of data that conforms to the normal distribution will be expressed as mean ± SD, the measurement data that does not conform to a normal distribution will be expressed by the median (interquartile range), and counting data will be represented by cases (percentages). The continuous variables will be evaluated by using a *t* test or the Mann-Whitney *U* test for comparison. The chi-square test or Fisher’s exact test will be employed to compare binary variables. Missing data will be imputed using the last observation carried forward.

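### The primary SBP comparison is valid on average but ignores baseline SBP; adjusting for it would add precision and remove the effect of chance imbalance at almost no cost

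*Protocol article*

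**What the plan says.** All references are to the protocol article.

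- **Primary outcome:** "The primary outcome will be the change in mean SBP from baseline to 12 weeks". The endpoint is a change score, so baseline SBP is collected for every participant.
- **Statistical analysis:** "The continuous variables will be evaluated by using a *t* test or the Mann-Whitney *U* test for comparison", "with a 2-sided *P* value of less than 0.05 considered significant", on an intention-to-treat basis. No covariate, regression or mixed model is named for any outcome.
- **Randomization and allocation concealment:** 1:1 allocation, "using block random method and the block size is 6". The stated purpose of the prepared sequence is "to ensure balance in baseline BP across the groups". No stratification or minimization on BP is described.
- **Inclusion criteria:** SBP from 120 to 140 mmHg, DBP from 80 to 90 mmHg, or both, at two or more visits.
- **Sample size:** "We selected the maximum of 30 participants, and the sample size of 60 participants was determined". The intended use is "The results of this study will facilitate the calculation of an appropriate sample size for further randomized clinical trials".

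**The concern.** An unadjusted test on change fixes the slope of week-12 SBP on baseline SBP at exactly 1. If the real slope is lower, subtracting the whole baseline over-corrects. The arm that starts higher by chance then appears to fall further, and the change score carries noise that a fitted slope would remove. People who qualify by their BP readings are open to regression to the mean, so a slope below 1 is likely here.

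The article itself wants the arms balanced on baseline BP. The device it describes, blocks of 6, equalizes the numbers per arm and does nothing for BP.

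At stake is the quality of the effect estimate and of the SD that the pilot is meant to hand to the next trial. The trial's false-positive rate is not at stake.

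**Working it through.** **The plan's own figure.** 2 arms × 30 = 60. This is a rule of thumb ("The minimum sample size for exploratory trials is 20 to 30 per group according to Provisions for Drug Registration in China"). The article gives no SD, correlation, effect size or power, so every SD, correlation and slope below is an assumption shown as a range.

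**1. Chance of a baseline imbalance.** With simple or blocked allocation, SE of the baseline difference = SD × √(2/30) = 0.258 SD.

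| Assumed baseline SD (mmHg) | SE (mmHg) | Chance that the difference exceeds 2 mmHg |
|---|---|---|
| 6 | 1.55 | 20% |
| 7 | 1.81 | 27% |
| 8 | 2.07 | 33% |

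At an SD of 5 mmHg, possible if the entry band cuts the spread hard, the chance falls to 12%.

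**2. What an imbalance does to the result.** If β is the slope of week-12 on baseline SBP, a baseline difference d shifts the change-score comparison by (1 − β) × d in size.
- β = 0.65: 0.35 × 2 = 0.7 mmHg
- β = 0.5: 0.5 × 2 = 1.0 mmHg

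A simulation of 20,000 trials (30 per arm, SD 8 mmHg at both times) agrees. The change-score estimate moved with baseline imbalance at slopes of −0.70, −0.51 and −0.30 for correlations of 0.3, 0.5 and 0.7. The ANCOVA estimate moved by about 0. Type I error was 0.048 to 0.052 for both methods.

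**3. Precision.** Per participant, with σ_b the baseline SD and σ_y the week-12 SD:
- change score: σ_y² + σ_b² − 2βσ_b²
- ANCOVA residual: σ_y² − β²σ_b²
- variance saved: (1 − β)²σ_b², which vanishes at β = 1

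*If the entry band truncates baseline SBP* (σ_b smaller than σ_y):
- σ_b = 6, σ_y = 9, β = 0.65: change variance 81 + 36 − 46.8 = 70.2; saved 0.1225 × 36 = 4.41; 4.41/70.2 = 6%
- σ_b = 6, σ_y = 10, β = 0.5: change variance 100 + 36 − 36 = 100; saved 0.25 × 36 = 9; 9/100 = 9%

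Simulated populations selected on two visits (baseline SD 5 to 9, follow-up SD 8 to 11, correlation 0.23 to 0.58) gave variance ratios of 0.91 to 0.94, which is the same range. In sample-size terms, 30/0.94 = 32 and 30/0.91 = 33 per arm. The confidence interval narrows by 3 to 5% (√0.94 = 0.97, √0.91 = 0.95).

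*If the two SDs are equal*, β equals the correlation ρ and the variance ratio is (1 + ρ)/2:
- ρ = 0.3: 0.65, a 35% reduction
- ρ = 0.6: 0.80, a 20% reduction

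*Cost of estimating the slope.* At N = 60 this multiplies the ANCOVA variance by about 1 + 1/56 = 1.018. The equal-SD ratios become 0.66 and 0.81. If β is near 1, the net gain is nil or a very small loss.

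Which case applies depends partly on how baseline is taken. A baseline reading separate from the qualifying visits is not truncated directly and lies nearer the equal-SD case. A baseline that averages the qualifying readings has a slope closer to 1, and the gain is then about nil.

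**4. Sizing the next trial.** For illustration, take equal SDs of 8 mmHg, a 5 mmHg difference and 80% power. The unadjusted change SD leads to 57 per arm against 37 for ANCOVA at ρ = 0.3, and 41 against 31 at ρ = 0.5. In the truncated case the gap is much smaller, in line with the 6 to 9% above.

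**The case against.** The strongest reply is that nothing here is an error. A t test on change scores is a legitimate analysis, unbiased over repeated randomizations, with type I error near 0.05. That stands: the loss is one of efficiency, plus bias conditional on the imbalance that happens to occur. It does not remove the case for a nearly free improvement.

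Four stronger readings are tempting, and the article does not support them.

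- **A large precision loss.** Under equal SDs, the 0.65 and 0.80 ratios correspond to about 46 and 38 per arm instead of 30. Selection on a BP band tends to make the SDs unequal, and the gain is then only 6 to 9%. The entry rule also admits people on DBP alone, so truncation of SBP is incomplete. Qualifying at two visits and averaging two readings both limit regression to the mean. A slope below 1 is likely, but how far below is not shown.
- **Allocation was unstratified.** A reader might infer this, but the article only fails to describe stratification. It is a condensed account that states balance in baseline BP as an aim. If the sequence was in fact stratified on BP, the imbalance probabilities above fall.
- **The test will be picked on observed normality.** The article ties normality to the descriptive summaries and gives no rule for choosing between the two tests. Such a rule may sit in an analysis plan that is not shown.
- **The pilot cannot size the next trial.** A change-score SD is the right input for a later change-score trial and is conservative for an ANCOVA trial. The team could also estimate the residual SD from the same data. A Mann-Whitney result alone, however, supplies neither a mean difference nor an SD.

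**Conclusion.** The point holds as a recommended improvement to a stated choice of method. The unadjusted comparison is valid on average, but it gives up precision and leaves part of any chance baseline SBP difference in the estimate whenever the slope is below 1. The balance the article aims for is not delivered by the only mechanism it describes.

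The imbalance risk is material for a trial of 60: roughly one in five to one in three for more than 2 mmHg, if the SD is 6 to 8 mmHg and allocation is not stratified on BP. The resulting shift is modest, and the precision gain ranges from close to nil to about a third. The truncated-baseline figure of 6 to 9% is the one to plan on unless the baseline reading is separate from the qualifying visits. Since the article supplies no SD, correlation or slope, no single number can be claimed.

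**What to change.** Make the primary analysis a linear model (ANCOVA) of week-12 SBP, or equivalently of change in SBP, on group with baseline SBP as covariate. Report the adjusted mean difference with its 95% CI, and the residual SD for sizing the next trial. Analyse DBP, SF-12, BMI and waist circumference in the same way, each with its own baseline. Keep the t test or Mann-Whitney test as a sensitivity analysis. If the sequence was stratified on BP, say so.

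The cost is one sentence and one degree of freedom, with no new data. Timing needs care: under Trial status all 60 participants were already randomized and follow-up was expected to end in November 2020, and the article appeared in February 2021. If the data are already unblinded, report the adjusted analysis and label it as added later.

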## Discussion

This manuscript presents the design of a randomized controlled pilot trial testing the effectiveness and safety of TEAS combined with lifestyle modification to improve BP control. To the best of our knowledge, there is no literature that has reported the effectiveness of TEAS combined with lifestyle modification on high-normal BP has been published.

Numerous studies have confirmed that high-normal BP is highly prevalent and increases the risk of incident hypertension, cardiovascular events, and death [7]. In China and other low-income and middle-income countries, long-term medication is costly to control BP. The intervention for the trial is innovative. For individuals with high-normal BP, exploring non-pharmaceutical therapies is feasible and necessary. Domestic TEAS may be an appropriate form of intervention. TEAS will be performed by the participants themselves at home, reducing transportation costs and possibly increasing compliance. Study investigators will ensure the participants fully understand the operation of TEAS. The education of lifestyle modification based on a commonly used social media software is also low cost. Therefore, the intervention model is characterized by accessibility, flexible, and low cost.

A limitation in the present study is the failure to clarify the optimal frequency of electrical stimulation of TEAS. Second, the participants are not blinded to the nature of intervention. At the end of this pilot trial, the results will potentially provide evidence of the feasibility and effectiveness of TEAS combined with lifestyle modification for high-normal BP and, if effective, a future large clinical definitive randomized controlled trial will be conducted.

### Trial status

Protocol: version 2.0, 30 June 2019.

The first patient was recruited on 6 September 2019. At the present time, a total of 60 patients had been randomized. The final date of follow-up is expected to be November 2020. This protocol was submitted prior to the recruitment of total 60 patients.

## Data Availability

The datasets analyzed during the current study are available from the corresponding author on reasonable request.

## Abbreviations

TEAS: Transcutaneous electrical acupoint stimulation
BP: Blood pressure
CVD: Cardiovascular disease
SDP: Systolic blood pressure
DBP: Diastolic blood pressure
SF-12: 12-Item Short Form Health Survey
IPAQ: International Physical Activity Questionnaire
BMI: Body mass index
AEs: Adverse events
CRA: Clinical research associate
ITT: Intention-to-treat
